## Abstract

**Background:**

There is scope to improve the quality of life (QOL) of people with dementia living in residential care facilities (RCF). The DIRECT study will determine if delivery of education to General Practitioners (GPs) and care staff improves the quality of life of residential care recipients with cognitive impairment.

**Methods/Design:**

A prospective randomised controlled trial conduced in residential aged care facilities in the metropolitan area of Perth, Western Australia. Participants are care facility residents, aged 65 years and older and with mini-mental state examination scores less than 25. GPs and care facility staff have been independently randomised to intervention or control groups. An education programme, designed to meet the perceived needs of learners, will be delivered to GPs and care staff in the intervention groups. The primary outcome of the study will be quality of life of the people with dementia, measured using the QOL-Alzheimer's Disease Scale (QOL-AD) and Alzheimer Disease Related QOL Scale (ADRQL), 4 weeks and 6 months after the conclusion of the education intervention.

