### Outcomes

Outcomes will be measured by blinded research assistants. Research assistants have been trained in the standard administration of assessment tools and adequate inter-rater reliability established for the QOL-AD [17].

The primary outcome of the study is the quality of life of the residents, measured using the (Alzheimer Disease Related QOL Scale (ADRQOL) [18] which relies on caregiver interview, and the QOL-Alzheimer's Disease Scale (QOL-AD) modified for use in long--term care settings [19,20] which utilizes self report and caregiver interview. Secondary outcomes include behavioural and psychologic symptoms of dementia (measured with the Neuropsychiatric Inventory- NH version [21]), use of restraint, and pain (measured using the Brief Pain Inventory modified verbal form [22]). Outcomes will be assessed at 4 weeks and 6 months after the conclusion of the educational intervention.

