### Sample size and statistical analysis

Training for care providers has been associated with a 0.4 point mean fall in QOL scores (SD 7.6) over 6 months, while QOL fell by a mean of 3.5 points (SD 7.9) in facilities that did not train care providers [10]. We have powered the present study to detect an effect of at least this magnitude. We would need 100 subjects in each row of the two by two factorial table (total number 200) to have 0.8 power to detect a main effect of this magnitude (alpha = 0.05; two sided). Loss of subjects to follow up, based on our previous experience, was anticipated to be in the order of 30% per annum in this population [23]. We used an estimated intra-class correlation of 0.05 (to account for clustering) and estimated cluster size of 9, resulting in an inflation factor of 1.4. We thus expected to have to enrol 364 subjects in forty clusters to achieve adequate numbers of completing subjects. This estimate of the intraclass correlation was conservative, given that intraclass correlation coefficients are typically smaller than 0.02 [24]. The power calculation was reviewed prior to closing recruitment, because actual cluster size (which influences the required number of participants) can be difficult to predict. Having recruited 67 clusters with an average cluster size of 5.2, it was confirmed that, because cluster size was smaller than anticipated, recruitment could be closed. Analysis will be by "intention to treat" (that is, according to randomisation, rather than participation in education). Statistical analysis will be conducted using multilevel mixed-effects linear regression in Stata version 11.0 (StataCorp, College Station, Texas). The effect of clustering by both facility and GP will be accounted for by treating the facility and GP as random effects with GP nested within facility. For each outcome analysis, a model containing the GP intervention, the facility intervention, and the baseline values of outcome variables will be used to estimate the marginal effect of each intervention. Next, the confounding effects of other covariates will be examined by comparing the adjusted and unadjusted intervention effects. Any covariates that produce clinically important changes in the intervention effect estimates, and are therefore demonstrably confounding these effects, will be retained in the model. Secondary analyses will be conducted to test the significance of any interaction between the facility and GP interventions. The results reported will include the estimated mean of the outcome variable in each arm of both interventions and for each intervention, the mean difference in outcome between the intervention and control arms. The results of the secondary analysis of the interaction between interventions will also be presented. All results will be presented with their associated 95% confidence intervals.

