**Figure 1 F1:**
[figure not shown]
**Study Flow Chart**.

**Table 1 T1:** Participant Characteristics.

Variable	First Follow-up Completed n = 288	Lost at First Follow Up n = 63	p
Age	85.1 ± 7.9	86.1 ± 7.8	0.367

Gender (Male)	58 (20%)	28 (44%)	0.000

MMSE	14 (6-20)	12 (8-18)	0.326

Weight (kg)	62.1 ± 14.0	63.6 ± 14.9	0.434

Self Rated QOL-AD	41.1 ± 6.00	42.3 ± 5.7	0.381

Staff Rated QOL-AD	32.5 ± 7.6	30.2 ± 6.5	0.017

NOK Rated QOL-AD	32.4 ± 8.1	32.4 ± 9.1	0.972

Staff Rated ADRQL	73.5 ± 16.5	69.7 ± 15.4	0.096

NOK Rated ADRQL	74.8 ± 14.5	75.2 ± 15.5	0.893

Number of medications	9 (7-12)	11 (8-13)	0.047

10 Item NPI	13 (4-29)	12 (4-26)	0.927

12 Item NPI	14 (5-32)	16 (6-27)	0.860

10 Item NPI Distress	4 (0-10)	3 (0-8)	0.431

12 Item NPI Distress	4 (1-11)	4 (1-8)	0.670

Values are mean ± SD or median (IQR); MMSE = mini-mental stare examination score, NOK= next of kin, ADRQOL = Alzheimer Disease Related QOL Scale, QOL-AD = QOL-Alzheimer's Disease Scale modified for use in long--term care settings, NPI = Neuropsychiatric Inventory- NH version [21]

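### The primary outcome is two scales at two times, with up to five rater versions and no lead measure, while the trial is powered for one unnamed QOL score at two-sided 0.05

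*Protocol article*

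**What the plan says.** All references are to the protocol article.

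- **Primary outcome.** The abstract (Methods/Design) speaks of the primary outcome in the singular, then gives two scales and two visits: the QOL-Alzheimer's "Disease Scale (QOL-AD) and Alzheimer Disease Related QOL Scale (ADRQL), 4 weeks and 6 months after the conclusion of the education intervention". The Outcomes section repeats both scales and both visits.
- **Raters.** The Outcomes section says that ADRQL comes from caregiver interview and describes QOL-AD as a scale "which utilizes self report and caregiver interview". Table 1 splits these into five versions: self, staff and next-of-kin QOL-AD, then staff-rated ADRQL and "NOK Rated ADRQL".
- **Sample size.** The section Sample size and statistical analysis starts from a "0.4 point mean fall in QOL scores (SD 7.6) over 6 months" with training, while "QOL fell by a mean of 3.5 points (SD 7.9) in facilities" without it. The scale and rater are not named. The target is "0.8 power to detect a main effect of this magnitude", at "alpha = 0.05; two sided", with 100 residents per row.
- **Analysis.** The same section fits one model for each outcome, estimates both intervention effects in it, and attaches a 95% interval to every result. It does not say which outcome leads.
- **Status.** The Results section reports that first follow-up is complete, second follow-up is under way and the analysis is still blinded.

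**The concern.** A singular primary outcome that contains several scales, raters and times does not say which estimate answers the trial's question. If one of them excludes zero and the others do not, nothing in the article settles whether education worked. The Discussion expects self and informant views to differ. Table 1 bears this out at baseline: among residents who completed first follow-up, mean QOL-AD is 41.1 by self, 32.5 by staff and 32.4 by next of kin.

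Two things are at stake. The false-positive rate of the primary claim exceeds the 0.05 used for planning. The power statement also cannot be tied to any one measure. The planning SDs are 7.6 and 7.9; baseline SDs in Table 1 run from about 6 to 9 for QOL-AD but from 14.5 to 16.5 for ADRQL, so a 3.1-point difference need not mean the same on both scales. (The planning SDs describe change and those in Table 1 describe baseline level, so this comparison is only indicative.)

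**Working it through.** **1. Reproduce the planned size.** Inputs from Sample size and statistical analysis: changes of -0.4 (SD 7.6) and -3.5 (SD 7.9), two-sided 0.05, power 0.8.

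- Difference = 3.5 - 0.4 = 3.1. Pooled SD = sqrt((7.6² + 7.9²)/2) = 7.75.
- n per row = 2 × (7.75/3.1)² × (1.960 + 0.842)² = 98.1, so 99. The article states 100.
- At 100 per row, SE = 7.75 × sqrt(2/100) = 1.096 and 3.1/1.096 = 2.83. Power = Φ(2.83 - 1.96) = 0.81.
- Enrolment: 200 × 1.4 × 1.3 = 364, as stated.

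The plan's figure therefore reproduces for one comparison at 0.05, with no allowance for more than one.

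**2. Count the primary comparisons per intervention.**

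- Minimum reading: 2 scales × 2 times = 4.
- All versions in Table 1: (3 QOL-AD + 2 ADRQL) × 2 times = 10.

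**3. Chance of at least one false positive, each comparison read at two-sided 0.05.**

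Independent: 1 - 0.95^k, which is 0.185 for k = 4 and 0.401 for k = 10.

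Equal pairwise correlation ρ: 1 - E[{Φ((1.96 - √ρ·U)/√(1-ρ)) - Φ((-1.96 - √ρ·U)/√(1-ρ))}^k], with U standard normal. The one-direction column drops the second term. The article gives no correlations, so ρ is an assumption.

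| k | ρ | Any result | In favour of education |
|---|---|---|---|
| 4 | 0 | 19% | 10% |
| 4 | 0.5 | 16% | 8% |
| 4 | 0.7 | 13% | 7% |
| 10 | 0 | 40% | 22% |
| 10 | 0.5 | 29% | 14% |
| 10 | 0.7 | 21% | 11% |

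As a sensitivity check, a structure with separate correlations between measures, within rater and over time, all between 0.2 and 0.8, gives 19-35% for k = 10.

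**4. Cost of keeping five versions primary at one time.** The strictest Holm step is 0.05/5 = 0.01, with critical value 2.576. Power at 100 per row, before clustering, is Φ(2.83 - 2.576) = 0.60, against 0.81 at 0.05.

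**5. Does the 6-month visit match the planning horizon?** The planning effect is a change over 6 months. The abstract's Results dates recruitment from May 2007 to July 2008 and education from September 2008 to July 2009, and the later visit is 6 months after education ends. If baseline was taken around recruitment (its exact dates are not given), a site that finished education in September 2008 would reach this visit in March 2009, 8 months after recruitment closed. A site that finished in July 2009 would reach it in January 2010, 18 months after. The two horizons do not match.

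**The case against.** Several points on the other side have force.

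- **No testing rule is written for the primary outcome.** Alpha appears only in the power calculation. The planned output is mean differences with 95% intervals, and significance testing is named only for the interaction. This stands: 0.05 per comparison is inferred.
- **Table 1 does not designate endpoints.** It compares residents followed up with those lost, and next-of-kin ratings are never called primary. This stands too, which is why the four-comparison reading is given first.
- **Multiplicity rules often sit in a SAP, which is not shown here.** A missing adjustment rule is therefore not the point. The multi-part definition of the primary outcome is, because the article states it in both the abstract and the Outcomes section.
- **Several viewpoints are deliberate.** The Discussion argues that no QOL measure is universally accepted. That justifies measuring all versions, but it does not settle which one leads.
- **All intervention effects are to be reported with intervals.** This limits selective presentation, but it does not rank the outcomes.

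A reader might infer that a chance primary success is likely, citing 20 comparisons over both interventions and 1 - 0.95^20 = 64%. The document does not support that. Facility staff and GP education are independently randomised and powered as separate main effects, so they are naturally separate families. The 64% also needs independence, which is implausible for ratings of one construct in the same residents at two visits, and it counts chance harm as success. Even over all 20 comparisons, a chance result favouring education is 40% if independent and about 18-32% under the assumed correlations.

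**Conclusion.** The point holds as a badly fixed primary outcome. The article defines it as two scales at two times, shows up to five rater versions, names no lead, and plans its size for one unnamed QOL score.

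Per intervention, the chance of at least one false-positive primary result is 13-19% on the minimum reading and 21-40% on the fullest. That is roughly 2.6 to 8 times the nominal 5%. About half of these results would favour education.

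These figures assume no true effect on any version, each comparison read at two-sided 0.05, and correlations between 0.7 and 0. The error rate is clearly inflated, but a chance success is not more likely than not. The conclusion does not depend on pooling the two interventions, or on counting next-of-kin ratings as primary.

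**What to change.** Amend the Outcomes section while the analysis is blinded. For each main effect (facility staff education, GP education), name one scale, one rater and one follow-up time as primary. Make the other versions and the other visit secondary, and say which measure the planning effect of 3.1 points refers to.

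The 6-month visit can be chosen in order to test a sustained effect, an aim the Discussion already gives. It should not be justified as matching the 6-month planning change, because it falls well over 6 months after baseline.

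If several versions must stay primary, restrict them to one time and apply Holm within each intervention.

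The cost of the first option is amendment wording and the loss of primary status for the other versions. Under the second, power at the strictest of five steps falls from about 0.81 to about 0.60 at 100 per row before clustering, and the amendment should say so.

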**Results:**

Recruitment of 351 people with dementia, cared for by staff in 39 residential facilities and 55 GPs, was undertaken between May 2007 and July 2008. Collection of baseline data is complete. Education has been delivered to GPs and Care staff between September 2008 and July 2009. Follow- up data collection is underway.

**Discussion:**

The study results will have tangible implications for proprietors, managers and staff from the residential care sector and policy makers. The results have potential to directly benefit the quality of life of both patients and carers.

**Trial registration:**

These trial methods have been prospectively registered (ACTRN12607000417482).

## Background

Many Australians with dementia, nearly half, live in residential care [1]. A large proportion of RCF residents have dementia, the majority with moderate-severe dementia [2-4]. However only a small proportion of beds are dementia-specific, and these have usually been designed to deal with specific behavioural and psychological challenges associated with dementia, such as frequent wandering [1].

Little is known about the subjective experience of people with dementia living in residential care. The available data suggest that people with moderate to severe dementia frequently experience distressing emotions [5]. Thus, there appears to be much scope to improve the experiences of residential care recipients.

Many of the common challenges encountered in caring for people with dementia can be ameliorated. For example behavioural treatments and non pharmacological interventions may reduce sleep and behavioural disturbances [6-8]. Changes to existing models of care, such as implementation of protocols to engage family caregivers, and environmental changes, may be effective in slowing residents' deterioration [9]. Likewise, there are data confirming that high quality care is associated with a lower incidence of depression [10].

Education and training appear to be effective in improving care outcomes. The introduction of dementia programmes in mainstream Australian hostels is thought to have been effective in delaying transfer to higher level care and in improving quality of life [11]. Education of nursing assistants and ancillary staff can improve their attitudes and knowledge regarding end of life care [12]. Training and support for nursing home staff is effective in reducing the proportion of residents with dementia who are prescribed neuroleptic medications (average reduction in neuroleptic use 19.1%; 95% confidence interval 0.5% to 37.7%) [13]. A marked reduction in psychotropic prescribing in Sydney nursing homes occurred in line with educational interventions and publicity regarding inappropriate medication use [14].

Cross sectional data suggest that staff training and specialisation are associated with improvements in the quality of life of people with dementia living in residential care [15]. However our data confirm that, despite staff and GPs working in residential care frequently participating in education and generally perceiving their knowledge as good, perceived educational needs persist [16]. The most effective way to translate the available evidence to practice is not clear and there is a paucity of prospective data to guide practice. The Dementia in Residential Care: education intervention Trial ("DIRECT") will determine if an educational intervention, designed in light of the perceived needs of learners, will enhance the quality if life of care recipients.

## Methods

### Study Design and Setting

DIRECT is a prospective randomised controlled trial conducted in residential aged care facilities of the metropolitan area of Perth, Western Australia.

### Participants

Inclusion criteria are i) permanent resident of a low-level or high-level residential care facility; ii) greater than 65 years of age; and iii) MMSE score ≤24. Exclusion criteria are i) participant's general practitioner works at more than one facility participating in the trial; ii) subject is identified by facility as medically unstable or as suffering delirium, or in the terminal stages of a co-morbid illness; iii) subject unable to participate in assessment instruments in English.

All residential care facilities (RCFs) in the Perth metropolitan area (n = 184) were sent information packages regarding the DIRECT Study. Of those, 36 agreed to participate. Participating RCFs compiled a list of residents to be screened for study participation. GPs working at the facility and residents meeting the inclusion criteria were invited to participate in the study. Study staff made second attempts to recruit GPs if residents they cared for had agreed to study participation, but the GP had not responded to the initial contact.

### Randomisation

Randomisation will be carried out in a factorial fashion. That is care facilities and GPs will be independently randomised to intervention or control groups. Allocation will be by a centrally held computer generated randomisation table, managed by an independent statistician.

### Intervention

A detailed qualitative research study has been undertaken to determine the perceived needs of learners [16]. This informed development of an educational package which was delivered to GPs, clinical and direct care staff between September 2008 and July 2009. The main topics of the educational programs were:

• communication with residents and family members

• personal care and activities

• positive values

• behaviours of concern

• pain management

• dementia, depression and delirium

• effective working between GPs and RCF.

The GP education program consisted of five modules, delivered during three evening sessions. A fourth, reflective, session was also held. The sessions used case scenarios from DVDs and role plays with volunteers and professional actors to stimulate participation, consistent with adult learning principles. They were facilitated by study staff and one or two of the authors. A self-directed learning package (DVD of the first three sessions plus supporting materials), and a reflection session, were offered to GPs not attending face-to-face workshops. The GP program was approved for 40 Category 1 Continuing Professional Development points for the 2008-2010 triennium. The RCF education intervention comprised 27 brief modules which were delivered on-site at each facility by one of two educators. This format was chosen to facilitate flexibility in delivery of the program. Each of the 27 lessons was in half hour blocks which could be built into sessions of varying lengths of time. Education sessions ranged from 1 hr blocks to full 7.5 hr days.

### Outcomes

Outcomes will be measured by blinded research assistants. Research assistants have been trained in the standard administration of assessment tools and adequate inter-rater reliability established for the QOL-AD [17].

The primary outcome of the study is the quality of life of the residents, measured using the (Alzheimer Disease Related QOL Scale (ADRQOL) [18] which relies on caregiver interview, and the QOL-Alzheimer's Disease Scale (QOL-AD) modified for use in long--term care settings [19,20] which utilizes self report and caregiver interview. Secondary outcomes include behavioural and psychologic symptoms of dementia (measured with the Neuropsychiatric Inventory- NH version [21]), use of restraint, and pain (measured using the Brief Pain Inventory modified verbal form [22]). Outcomes will be assessed at 4 weeks and 6 months after the conclusion of the educational intervention.

### Sample size and statistical analysis

Training for care providers has been associated with a 0.4 point mean fall in QOL scores (SD 7.6) over 6 months, while QOL fell by a mean of 3.5 points (SD 7.9) in facilities that did not train care providers [10]. We have powered the present study to detect an effect of at least this magnitude. We would need 100 subjects in each row of the two by two factorial table (total number 200) to have 0.8 power to detect a main effect of this magnitude (alpha = 0.05; two sided). Loss of subjects to follow up, based on our previous experience, was anticipated to be in the order of 30% per annum in this population [23]. We used an estimated intra-class correlation of 0.05 (to account for clustering) and estimated cluster size of 9, resulting in an inflation factor of 1.4. We thus expected to have to enrol 364 subjects in forty clusters to achieve adequate numbers of completing subjects. This estimate of the intraclass correlation was conservative, given that intraclass correlation coefficients are typically smaller than 0.02 [24]. The power calculation was reviewed prior to closing recruitment, because actual cluster size (which influences the required number of participants) can be difficult to predict. Having recruited 67 clusters with an average cluster size of 5.2, it was confirmed that, because cluster size was smaller than anticipated, recruitment could be closed. Analysis will be by "intention to treat" (that is, according to randomisation, rather than participation in education). Statistical analysis will be conducted using multilevel mixed-effects linear regression in Stata version 11.0 (StataCorp, College Station, Texas). The effect of clustering by both facility and GP will be accounted for by treating the facility and GP as random effects with GP nested within facility. For each outcome analysis, a model containing the GP intervention, the facility intervention, and the baseline values of outcome variables will be used to estimate the marginal effect of each intervention. Next, the confounding effects of other covariates will be examined by comparing the adjusted and unadjusted intervention effects. Any covariates that produce clinically important changes in the intervention effect estimates, and are therefore demonstrably confounding these effects, will be retained in the model. Secondary analyses will be conducted to test the significance of any interaction between the facility and GP interventions. The results reported will include the estimated mean of the outcome variable in each arm of both interventions and for each intervention, the mean difference in outcome between the intervention and control arms. The results of the secondary analysis of the interaction between interventions will also be presented. All results will be presented with their associated 95% confidence intervals.

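### The enrolment target of 364 allows for 30% loss by multiplying by 1.3 where division by 0.7 (giving 400) was needed; the practical effect is small, but 6-month power for the facility effect is left unsettled

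*Protocol article*

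**What the plan says.** All under Protocol article, Sample size and statistical analysis, unless another section is named.

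- **Effect and SDs.** Both come from a cited comparison of facilities. Training was "associated with a 0.4 point mean fall in QOL scores (SD 7.6) over 6 months". The corresponding fall without training is given as 3.5 points, SD 7.9.
- **Number before inflation.** 100 residents on each side of a main effect, expressed as "total number 200) to have 0.8 power to detect a main effect of this magnitude (alpha = 0.05; two sided".
- **Clustering.** Intraclass correlation 0.05 and cluster size 9, giving a factor of 1.4.
- **Loss.** "anticipated to be in the order of 30% per annum in this population".
- **Conclusion.** "We thus expected to have to enrol 364 subjects in forty clusters to achieve adequate numbers of completing subjects".
- **Later review.** The calculation was looked at again before recruitment closed, with 67 clusters averaging 5.2 residents, and closure was judged acceptable. No revised target, completer number or power is printed.
- **Calendar.** Recruitment "was undertaken between May 2007 and July 2008" (Abstract, Results). Education was "delivered to GPs, clinical and direct care staff between September 2008 and July 2009" (Intervention). "Outcomes will be assessed at 4 weeks and 6 months after the conclusion of the educational intervention" (Outcomes).
- **Delivered so far.** 39 facilities and 55 GPs (Results). Table 1 shows 288 residents with a completed first follow-up and 63 lost, 351 in all.

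**The concern.** The target is presented as what is needed to finish with enough residents for 0.8 power. If 30% are lost, the number enrolled must be the number of completers divided by 0.7. Multiplying by 1.3 always gives too few: 1.3 × 0.7 = 0.91, so 9% of the required completers are missing.

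Two further points bear on the 6-month visit, which is one of the two primary time points. The loss rate is per year, while the calendar points to more than a year between enrolment and the last visit for many residents. And the review that supported closing recruitment used a cluster size that does not describe the facilities, although facilities are one of the two randomised units.

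At stake is how a null 6-month result is read. The article sets it against 0.8 power, and the printed calculation does not establish that figure.

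**Working it through.** **Inputs.** Difference 3.5 − 0.4 = 3.1 points; SDs 7.6 and 7.9 (pooled 7.75); two-sided alpha 0.05; intraclass correlation 0.05; planned cluster size 9; loss 30% per year. All come from the sample size section.

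**1. Number before inflation.** n per group = (1.96 + 0.8416)² × (7.6² + 7.9²)/3.1² = 98.1. The stated 100 is right. With power = Φ(3.1/(7.75 × √(2/n)) − 1.96), n = 100 gives 0.81.

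**2. Clustering.** 1 + (9 − 1) × 0.05 = 1.4, as stated. Implied completers: 200 × 1.4 = 280. The article does not print 280; it follows from the two stated figures.

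**3. Reproducing 364.** 280 × 1.3 = 364 exactly. The correct allowance is 280/0.7 = 400, which is 36 more.

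**4. What 364 delivers on these inputs.** 364 × 0.7 = 254.8 completers, about 25 short of 280. Effective number 254.8/1.4 = 182, or 91 per group; power 0.77. Enrolling 364 yields 280 completers only if loss is 1 − 280/364 = 23.1%.

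**5. The review before closure.** At cluster size 5.2 the factor is 1 + 4.2 × 0.05 = 1.21. Completers needed: 200 × 1.21 = 242. To enrol, with the correct division: 242/0.7 = 346. The roughly 350 enrolled meets this for one year's loss.

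**6. Why the review does not settle the facility effect.** 67 × 5.2 = 348, so its cluster size comes from 67 units. There are 39 facilities, and 351/39 = 9.0 enrolled residents each. For the facility main effect, the cluster size at enrolment is therefore the planned 9, not 5.2.

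**7. Delivered numbers.** First follow-up (4 weeks): 288 completers, loss 63/351 = 17.9%. Projected to 6 months, assuming five more months at 30% per year: 288 × 0.7^(5/12) = 248.

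**8. Facility effect at 6 months.** Completers per facility: 248/39 = 6.4. Factor: 1 + 5.4 × 0.05 = 1.27. Effective number about 196, or 98 per group; power about 0.80, before allowing for unequal cluster sizes. Keeping the factor at 1.4 would give 248/1.4 = 177 and power 0.76, but that charges clusters for members who are no longer in the analysis.

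**9. Calendar.** Where education ended in July 2009, the 6-month visit falls around January 2010: about 18 months after the last enrolment (July 2008) and 32 after the first (May 2007). Where it finished early, a late-enrolled resident could have under 12 months. The article gives neither end dates by facility nor a planned interval from enrolment to outcome.

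**The case against.** The best defence is that 364 was overtaken within its own section. Recruitment was closed on the later review, and step 5 shows that closure stands up for one year's loss even with the correct division. This holds for clusters of 5.2. It does not carry over to the 39 facilities, and no corrected figure or 6-month power was printed in its place.

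A second defence is that loss also shrinks clusters. With 364 in forty clusters, 30% loss leaves about 6.4 per cluster, a factor of 1.27 and a need for about 254 completers, which 254.8 just meets (power 0.81). That is a fair account of the impact. It is not how the plan calculated: the plan kept 1.4, and 364 matches multiplication by 1.3 exactly.

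Third, the inputs lean to the safe side. The article calls 0.05 conservative, with typical values below 0.02, and the model adjusts for baseline, which normally adds precision. Both points stand and support a low severity.

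Two stronger readings are tempting. A reader might infer that the trial is short of residents at both primary visits. At 4 weeks it is not: 288 exceeds even 280. A reader might also run 30% per year over 18 months and expect 351 × 0.7^1.5 = 206 completers, with power well below 0.8. Table 1 argues against this. Falling from 288 to 206 would mean losing about 29% in five months, roughly 55% per year. The realised calendar suggests long follow-up, but does not show that the planners knowingly applied one year's loss to a longer planned interval.

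**Conclusion.** The point stands as an arithmetic slip of minor severity. On the plan's own inputs the target should have been 400, and 364 corresponds to power of about 0.77 at factor 1.4 rather than 0.80.

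The effect on the trial as run is small. Enrolment of about 350 is enough for one year's loss at the reviewed cluster size, the 4-week visit has ample numbers, and power for the facility effect at 6 months comes out at about 0.80. That last figure assumes an intraclass correlation of 0.05, five more months of loss at 30% per year after first follow-up, completers spread evenly over 39 facilities, and no gain from baseline adjustment. Unequal cluster sizes would lower it; a smaller intraclass correlation or baseline adjustment would raise it.

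What remains open is a stated 6-month power for each main effect, based on the loss and cluster sizes that the trial actually has.

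**What to change.** Text only, with no further enrolment and no change to design or analysis.

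1. Add a note that 364 multiplied by 1.3 where division by 0.7, giving 400, was needed. Leave 364 on record as the target actually used.
2. State what the trial delivers: 351 enrolled, 288 at first follow-up, and about 248 projected at 6 months, with the projection's assumption beside it.
3. Give 6-month power separately for the facility and the GP main effects, each with the design effect at its own completing cluster size. For facilities: about 6.4 per facility, factor about 1.27, power about 0.80 before allowing for unequal cluster sizes.
4. State the interval from baseline to the 6-month visit, so that the annual loss rate can be read against it.

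The cost is a short paragraph. Results reports that second follow-up is still under way and the analysis remains blinded, so the note can be written before any result is known.
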